### Household contacts

To further investigate possible transmission links, household contacts of index cases presenting with blood culture-confirmed *S* Typhi or *S* Paratyphi A infection will be identified through the census data collection and approached to take part in this component of the study. Up to five members of the household, with consent, will be asked to provide a blood and stool sample at the time of discharge of the index case, a further stool sample at 1 month and repeat serology at 6 months (see online supplementary table 1), and asked about the occurrence of symptoms. These samples will be investigated to identify those with subclinical infection or possible chronic carriers. Secondary attack rates for the occurrence of symptomatic infection will be estimated. If serology suggests chronic carriage in a household contact, additional blood and stool samples will be collected to confirm this, and antimicrobial treatment to eradicate carriage will be proposed.

Those individuals who are identified as shedding bacteria but without high serum anti-Vi IgG levels will be followed up at a 1-year interval to repeat stool culture. Repeat blood samples will be collected from household contacts approximately 3 months after initial sampling to explore whether rates of seroconversion are higher in these individuals compared with those in the general population. At least 73 households of index cases are expected to be enrolled in this component of the study.

In a similar approach to the acute cases of typhoid infection, where chronic carriers are identified from the serosurveys, household transmission studies will be performed among household contacts of possible chronic carriers (ie, those with a ‘high’ serum anti-Vi IgG titre). A one-time attempt will be made to enrol up to five members of the household, sampling serology and stool looking for evidence of typhoid infection. This will provide data on secondary attack rates for both acute and chronic typhoid states.

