### Patan, Nepal

Patan is located within the Lalitpur Sub-Metropolitan City within the Kathmandu Valley, Nepal (figure 1C). The population is generally poor, with most living in overcrowded conditions and obtaining their water from stone spouts or sunken wells. Patan Hospital is a 318-bed government hospital providing emergency and elective outpatient and inpatient services to this area. The local catchment population of the hospital is approximately 200 000 people in about 20 km^2^, with a population density of 8000/km^2^; there is a high rate of immigration for employment, particularly young males from rural areas. Enteric fever is frequently managed in the outpatient clinic at Patan Hospital, which has approximately 200 000 outpatient visits annually.

Uptake of typhoid Vi vaccination is limited and natural exposure/subclinical infection is common.^29^ Approximately 400 culture-confirmed cases of enteric fever are diagnosed at Patan Hospital each year, with a peak during the monsoon months. The current *S* Typhi:Paratyphi A ratio is approximately 1:1.^54^ Antimicrobial resistance is more commonly observed in *S* Paratyphi A isolates; however, emergence of fluoroquinolone-resistant *S* Typhi isolates has also been recently identified,^55^ whereas MDR strains of either serovar are rare.^38^

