### Serosurveys

To estimate the seroincidence and seroprevalence of clinical (both formally diagnosed and undiagnosed cases) and subclinical infection or exposure to *S* Typhi and *S* Paratyphi, systematic serosurveillance will be performed at each site. Blood samples will be collected at baseline and 3 months later, with sample collection initiated in an ongoing basis over the course of 1 year (table 3). To identify participants for the serosurvey, an age-stratified approach will be used to randomly select individuals from the census population from each age group. Suitable participants will be enrolled by field workers; where the individual identified is not available, a household member in the same age group will be selected. Where this is not possible, further households will be randomised into this component to ensure adequate numbers of individuals in the different age groups.

**Table 3 T3:** Sample size calculations for the serological surveys to estimate age-specific rates of high titres of serum IgG anti-H(d) antibodies

	Anticipated seroincidence (%)	Initial samples (n)	Anticipated number of events	Follow-up samples (n)*	Events detected (n)	Binomial exact (95% CI)	Probability of observing 0 events
0–4 years	0.2	2500	5	2000	4	0.0005 to 0.0051	0.0182
5–9 years	0.4	1300	5.2	1040	4	0.0010 to 0.0098	0.0155
10–14 years	0.8	800	6.4	640	5	0.0025 to 0.0181	0.0059
>14 years	0.2	3900	7.8	3120	6	0.0007 to 0.0042	0.0019
Total		8500	24.2	6800	19		

Assumes age-stratified individual sampling; also accounts for detection of 1% chronic carriage rate in those aged ≥10 years.

*Assuming 5% migration and 15% refusal.

Seroincidence (indicative of recent infection) will be calculated by measuring the rate of seroconversion to anti-H(d) (anti-flagellin) IgG and other acute-phase antibodies between both time points, with the denominator consisting only of individuals sampled twice and seronegative at the first time point.^56^

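### First bleeding household contacts at the index case's discharge pulls their seroconversion comparison with the general population toward no difference

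*Protocol article*

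**What the plan says.** **Contacts.** In the protocol article, section Household contacts, up to five consenting members of an index household "will be asked to provide a blood and stool sample at the time of discharge of the index case". A household qualifies only once the index infection has been confirmed by blood culture. The section continues: "Repeat blood samples will be collected from household contacts approximately 3 months after initial sampling to explore whether rates of seroconversion are higher", with the general population as comparator. It separately plans stool at 1 month and "repeat serology at 6 months", and says of the contacts' samples: "These samples will be investigated to identify those with subclinical infection or possible chronic carriers".

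**General population.** In Serosurveys, participants are drawn at random from the census by age group. "Blood samples will be collected at baseline and 3 months later", with enrolment spread over a year, so the first bleed is not tied to any illness. Seroincidence is the rate of conversion to anti-H(d) IgG and other acute-phase antibodies, "with the denominator consisting only of individuals sampled twice and seronegative at the first time point".

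**Not stated.** Household contacts gives no denominator of its own and does not say how contacts already seropositive at their first sample enter the comparison. Nor does the article say what discharge means for an index patient who was never admitted, although the Patan section notes: "Enteric fever is frequently managed in the outpatient clinic at Patan Hospital".

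**The concern.** Seroconversion presupposes a negative first sample. For contacts, that sample comes after the exposure whose effect is being sought. Under Passive surveillance, an index patient has had more than 72 hours of reported fever or a temperature above 38.5°C at presentation, has been cultured, and must be culture-positive. A contact infected from the same source, or early on by the index case, may have crossed the antibody cut-off by discharge. Under the serosurvey's rule that contact leaves both numerator and denominator.

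The serosurvey also drops people who are positive at baseline, but its baseline is not timed to an exposure, so it does not selectively lose recent infections. The loss falls on the contacts' excess alone. It is structural, and more households would not cure it. At stake is one of the ways in which the study can learn whether living with a case raises the risk of infection.

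**Working it through.** **1. Comparator rate, from Table 3.** Follow-up n = initial n × (1 − 0.05 − 0.15) gives 2000, 1040, 640 and 3120. The probability of no events, (1 − p)^n, gives 0.0182, 0.0155, 0.0059 and 0.0019. Both match the table. Expected events are 4.00 + 4.16 + 5.12 + 6.24 = 19.52 in 6800, so the pooled rate is g = 19.52/6800 = 0.287%. I take this as the rate over the 3-month interval.

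**2. Number of contacts.** At least 73 households with up to five contacts gives 73 × 5 = 365. If the serosurvey's 20% loss applies (an assumption), 365 × 0.8 = 292 pairs. Background seroconversions among them: 292 × 0.00287 = 0.84. The article gives no sample-size calculation for this comparison.

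**3. Attenuation.** Let R be the true ratio and q the share of excess infections already seropositive at the first bleed. The article does not give q. Then

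observed ratio ≈ 1 + (R − 1)(1 − q)

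| True ratio R | q = 25% | q = 50% | q = 75% |
|---|---|---|---|
| 3 | 2.5 | 2 | 1.5 |
| 5 | 4 | 3 | 2 |
| 10 | 7.75 | 5.5 | 3.25 |

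**4. The same with the shrinking denominator.** Let π be the share of contacts infected around the index episode (also not given). Among contacts still seronegative at the first bleed, i = π(1 − q)/(1 − πq), and the observed rate is i + g(1 − i). Example with π = 1%, q = 50%: i = 0.005/0.995 = 0.00503; rate = 0.00503 + 0.00287 × 0.99497 = 0.00788; ratio = 0.00788/0.00287 = 2.7. Step 3 gives the same.

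| π (assumed) | q = 0 | q = 50% | q = 75% | q = 90% | q = 100% |
|---|---|---|---|---|---|
| 1% | 4.5 | 2.7 | 1.9 | 1.4 | 1.0 |
| 5% | 18.4 | 9.9 | 5.5 | 2.8 | 1.0 |

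The ratio always falls when q > 0, but reaches 1 only if every episode-related infection is already seropositive.

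**5. Rough power.** For 292 contacts against 6800, two-sided 5%, household clustering ignored:
- π = 1%: 69% at q = 0, 39% at q = 50%, 8% at q = 90%.
- π = 5%: about 100%, 97% and 40%.

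Events are few, so these are approximate, and clustering would lower them.

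**6. Where the lost infections can be seen.** With background seroprevalence s, contacts' expected first-sample seroprevalence is about s + (1 − s)πq. The serosurvey baseline estimates s, so the difference estimates (1 − s)πq, which is the part the seroconversion rate omits.

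**The case against.** - **The denominator is inferred.** The rule is written for the serosurvey, and neither the supplementary table nor an analysis plan is shown. This stands, and the point is conditional on carrying the rule over. It is, however, the only rule the article gives.
- **The target is not stated.** If only infection after the first bleed is wanted, excluding contacts already seropositive is ordinary incidence practice, and late seroconverters from a shared source would push the ratio up. This stands too. Attenuation follows only if all infection around the episode is meant.
- **The loss may be small.** A patient can enter on temperature alone after a short illness, so q could be low. The documents do not settle this.
- **The comparison is exploratory.** Table 1 does not list it as an objective. Stool cultures, symptom enquiry, secondary attack rates and the search for subclinical infection also bear on household transmission. Early-infected contacts leave one rate, not the study.

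Three stronger readings are tempting but unsupported. A reader might infer that every contact infected with or before the index case is lost, and the difference erased; in fact contacts infected but not yet seropositive still count. A reader might infer that other sites bleed contacts later than Patan, so that site differences in timing would look like differences in transmission. The article does not say when other sites sample, analyses countries separately, and adjusts for country when pooling. Finally, nothing says that a null result would be read as absence of household transmission.

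**Conclusion.** The point holds as a cheap improvement. If the serosurvey's denominator is applied to contacts and the comparison is meant to cover all infection around the index episode, the ratio is biased toward 1, but not to it. The direction follows from the sampling times. The size cannot be fixed from the article, because it depends on q and π: the fall of a true ratio of 5 to 4, 3 or 2 is an illustration, not an estimate. With under one background seroconversion expected in about 292 pairs, the comparison has few events to spare. Outpatient care at Patan is a secondary point: it leaves the anchor for the first contact visit unclear for some index cases, and the documents support no more than that.

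**What to change.** 1. Beside the seroconversion comparison, report contacts' first-sample anti-H(d) seroprevalence against the serosurvey baseline at the same site, standardised for age. Treat contacts seropositive at that sample as possible co-primary or early infections.
2. State the contacts' denominator, and that their seroconversion rate covers only infections becoming seropositive after the first bleed.
3. Secondary: tie the first contact visit to a date that every index case has, such as culture confirmation. This makes timing consistent across index cases. It does not remove the attenuation, since the bleed still follows the shared exposure and the index illness.

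The cost is one further analysis on samples already planned and two short changes of wording. The drawback is that first-sample seropositivity also includes older infection, which is why the comparator must be age-standardised. Age standardisation does not remove differences in past exposure between index households and others, so an excess should be described as possible, not proven, infection from the index episode.

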### Data management and analysis

Census and serosurvey data collection forms will be developed through a structured iterative process and then implemented using Open Data Kit,^59^ a system enabling electronic mobile data collection, with customisations by Nafundi, USA, on Android-based tablets. Each household within the census will be assigned a unique study ID and geo-located using GPS where possible; individuals will be given a member number within the household. This information will be collected by local enumerators over a 1–4-month period via these forms and adapted to the three geographic settings. Data will be uploaded onto MySQL databases, where SQL routines will be run nightly to enforce data cleaning on critical variables beyond ODK’s validation routines. Daily anonymised data will be backed up from the three sites centrally. For the passive surveillance and household contacts studies, a combination of tablet and paper-based case report forms will be used to capture the data. Data from paper forms will be transcribed onto electronic databases using Open Clinica.^60^ Database reports and descriptive analyses will be generated weekly. To assess efficiency and quality of data capture, the volume, accuracy and time of data collection can be quantified.

The distribution and burden of enteric illness is likely to vary between countries and thus analyses will be conducted separately for each country. Where data are combined across countries, an adjustment for country differences will be included in statistical models.

## Ethics

Written informed consent was obtained from the head of each household (as the ‘key informant’) on behalf of the entire household in the demographic census and healthcare utilisation surveys. In each of the other components, individual written informed consent was obtained from individuals over the age of 18 or by a parent/guardian from individuals below this age with additional assent sought from those aged between 11 and 17 years.

This protocol has received ethics approval from the Oxford Tropical Research Ethics Committee, the Malawian National Health Sciences Research Committee and University of Malawi Research Ethics Committee, the Nepal Health Research Council and the icddr, b Institutional Review Board.

## Dissemination

We hope to make the results from these studies widely available and plan to disseminate our analyses in international peer-reviewed journals. Investigators will be involved in reviewing drafts of the manuscripts, abstracts, press releases and any other publications arising from the study. Furthermore, data from these studies will also be used in the submission of postdoctoral theses.

## Community public engagement

A collection of specific activities engaging the local population with both the subject of typhoid fever and the activities of the study have been carried out. In Malawi, for example, community leaders have been informed and consulted on certain aspects of the study, shown the proposed activities of study teams and given tours of research facilities. There has been engagement with various forms of media disseminating information on the importance of typhoid and study aims. In Nepal, field staff have been given detailed information to communicate to the local populations.

Further activities are planned to ensure the local populations are informed and engaged.

## Discussion

The STRATAA study is a comprehensive multicentre study aiming to improve understanding of typhoidal *Salmonella* infection in high-risk endemic populations. This study has been designed to answer key questions and data gaps identified through an innovative application of recent mathematical modelling. These gaps include measuring the burden of age-stratified disease, identifying the relative contribution of asymptomatic/subclinical *Salmonella* infection/exposure and estimating the contribution to ongoing transmission from the chronic carrier state. These data will inform further modelling required to develop and optimise disease control and prevention strategies that will eventually lead to disease elimination.
